## Abstract

**Background:**

Treatment of depression, the most prevalent and costly mental disorder, needs to be improved. Non-concordance with clinical guidelines and non-adherence can limit the efficacy of pharmacological treatment of depression. Through pharmaceutical care, pharmacists can improve patients' compliance and wellbeing. The aim of this study is to evaluate the effectiveness and cost-effectiveness of a community pharmacist intervention developed to improve adherence and outcomes of primary care patients with depression.

**Methods/design:**

A randomized controlled trial, with 6-month follow-up, comparing patients receiving a pharmaceutical care support programme in primary care with patients receiving usual care. The total sample comprises 194 patients (aged between 18 and 75) diagnosed with depressive disorder in a primary care health centre in the province of Barcelona (Spain). Subjects will be asked for written informed consent in order to participate in the study. Diagnosis will be confirmed using the SCID-I. The intervention consists of an educational programme focused on improving knowledge about medication, making patients aware of the importance of compliance, reducing stigma, reassuring patients about side-effects and stressing the importance of carrying out general practitioners' advice. Measurements will take place at baseline, and after 3 and 6 months. Main outcome measure is compliance with antidepressants. Secondary outcomes include; clinical severity of depression (PHQ-9), anxiety (STAI-S), health-related quality of life (EuroQol-5D), satisfaction with the treatment received, side-effects, chronic physical conditions and socio-demographics. The use of healthcare and social care services will be assessed with an adapted version of the Client Service Receipt Inventory (CSRI).

**Discussion:**

This trial will provide valuable information for health professionals and policy makers on the effectiveness and cost-effectiveness of a pharmaceutical intervention programme in the context of primary care.

**Trial registration:**

NCT00794196

## Background

One of the main challenges of public health is to improve the treatment of depression. In fact, major depressive episode is one of the most prevalent mental disorders, both in the general population [1-3] and in primary care [4], and is one of the five mental disorders that cause the highest impairment, even higher than the ones associated with chronic physical conditions [5-7]. Furthermore, it is the most costly brain disorder in Europe, accounting for 33% of the total cost [8]. Even though pharmacological treatment in major depressive episodes is mostly prescribed as recommended by Spanish primary care physicians, percentages of treatment concordance with clinical guidelines are low (between 21% and 25%) mainly because recommended follow-up sessions are not performed [9]. Moreover, adherence to antidepressant medication is poor [10], which could limit its effectiveness in clinical practice. The World Health Organization and the European Council have stressed the importance of including community pharmacists, considered the health professional most readily accessible to patients, as an active member of the multidisciplinary healthcare team with the aim of benefiting patients' health [11,12], including those suffering from mental disorders [13].

By means of pharmaceutical care, community pharmacists have been shown to improve patient wellbeing in chronic physical conditions such as diabetes mellitus [14] and hypertension [15].

Research has been done to evaluate the effect of pharmaceutical care among outpatients diagnosed with depression [16-21] but in only three of the studies was the intervention conducted by a community pharmacist [16-18] and only one of them took place in a European country [16]. This was the only study that reported cost analysis information [22]. The results provided by these studies are contradictory and still more research is needed in order to study this issue. The aim of this study is to evaluate the efficacy of a pharmaceutical care programme, compared with usual care, on the improvement of adherence to antidepressant drugs and patient wellbeing in a population with a diagnosis of depression treated in primary care under real practice circumstances. Programme cost-effectiveness will be also calculated.

## Methods/design

We followed the CONSORT statement for reporting randomized trials [23].

6 month follow-up naturalistic randomized controlled trial with random allocation of participants into two alternative branches: 1) Usual medical and pharmaceutical care plus support programme in community pharmacy (intervention group), and 2) Usual medical and pharmaceutical care (control group) (Figure 1).

**Figure 1 F1:**
[figure not shown]
**Study design**.

The evaluation of compliance and clinical improvement of participants will be carried out by individual assessment at baseline, 3 and 6 months after the beginning of the intervention.

The Clinical Research Ethics Committee of the Foundation Sant Joan de Déu (CEIC *Fundación *SJD) approved the study protocol (Reference Number: BECAFIS04/07). Participants are only allowed to enter the study after signed informed consent has been obtained.

### Setting

Gavà is a city situated in the province of Barcelona (Catalonia, Spain) approximately 15 kilometres south of Barcelona city. With a total area of 30.9 square kilometres and a population of more than 45,000 inhabitants, the city has two primary care health centres (PCHCs) (Gavà-1 and Gavà-Doctor Bartomeu Fabrés Anglada) that provide medical care to the whole population of Gavà. Patients will be recruited at those PCHCs from October 2008 to October 2009. 23 general practitioners (GPs) from the PCHCs voluntarily participate in the study and deal with the identification and subsequent recruitment of the patients.

Altogether there are 14 community pharmacies in Gavà that were asked to participate in the study. In addition, there is a community pharmacy in the adjacent town of Viladecans located very near to one of the PCHCs that was also asked to participate. Two of the pharmacies (13%) refused to participate, one citing heavy workload and the other a lack of interest in the study. Finally, 13 pharmacies with a total of 34 pharmacists will be responsible for providing patients with the intervention and usual care during the 6 month follow-up period.

### Enrolment, randomization and allocation

All patients initiating a treatment with any antidepressant due to a depressive disorder through medical prescription from a PCHC GP in Gavà, and who are aged 18–75, are candidates for inclusion in the study. The following patients will be excluded: those on antidepressant medication in the past 2 months, those who had an appointment with an specialist in mental health in the past 2 months, those with history of psychotic or bipolar disorders, those with history of drug abuse or dependency, those with cognitive impairment that prevents assessment interviews, and those attending a pharmacy not included in the study. The eligibility criteria are listed in Table 1.

**Table 1 T1:** Eligibility criteria

**Patients...**
aged between 18 and 75,
initiating a pharmaceutical antidepressant treatment due to a depressive disorder through a medical prescription from a GP,
going to one of the participant community pharmacies,
that did not take antidepressant medication in the previous 2 months,
that have not had an appointment with an specialist in mental disorders in the previous 2 months,
with no history of psychotic or bipolar disorders,
with no history of drug abuse or dependency,
with no cognitive impairment that prevents assessment.

Patients meeting the inclusion criteria are given the information about the study's aim and procedures during the medical visit and written informed consent is obtained. With the informed consent, the GP registers the patient's telephone number and PCHC clinical-history reference number. Within a week of the inclusion date, baseline assessment is performed at the PCHC by a trained psychologist.

Randomization was generated at the patient level by a computerized random-number generator following a permuted block design. Block size was of 10 patients with a ratio of 1:1. To assure the concealment of allocation, every GP receives a set of 10 sequentially numbered, opaque, sealed envelopes containing patient assignment. Envelopes were generated by an external investigator and details of the series are unknown to any of the GPs or pharmacists in the study. As patients are enrolled, the GP sequentially staples one of the envelopes to the prescription. When the patient gives the prescription to their community pharmacist, they open the envelope and create a patient study chart distinguishing between control and intervention group.

Blinding of participants and pharmacists is not possible because of the type of intervention. However, the assessment visits and data analysis are conducted by independent and blinded evaluators.

### Intervention and usual care

Patients in the intervention group will receive the support programme in community pharmacy (PRODEFAR) every time they go to the pharmacy to pick up the medication or to ask for counselling in the course of the 6 months of the study. Pharmacists participating in the study received 8 hours of training about PRODEFAR prior to the study. The training followed a manual created for the study and is accredited by the Catalonian council of continuous pharmaceutical training (*Consell Català de la formació farmacèutica contínua*) (Reference Number: 09F00676).

PRODEFAR consists of a series of educational interventions focused on improving patients' knowledge of antidepressant medication, as well as making patients aware of the importance of compliance to the medication. Moreover, in patients with a sceptical attitude towards the medication, the intervention will aim to reduce stigma, reassure the patient about possible side-effects, and stress the importance of carrying out GPs' advice. First contact in the PRODEFAR is expected to take between 20 and 30 minutes, subsequent interventions are expected to take between 10 and 15 minutes.

Regardless of whether participants belong to the intervention group or not, they receive the usual pharmaceutical care as well as the treatment considered most appropriate by their physician. Patients receiving usual care get ordinary advice about medication when collecting it. Any concerns and questions addressed to the pharmacist are also answered.

Patients in the intervention group are asked to avoid conversations concerning the PRODEFAR with patients from the control group. The importance of this requirement is emphasised to patients from both groups at baseline assessment.

### Measurements

Three assessment visits – at baseline, 3 and 6 months – are conducted by independent and blinded interviewers. Participants, pharmacists and GPs are not blinded. To limit bias, two trained psychologists conduct all the interviews. [name] and [name] were responsible for the interviewers' training. Table 2 shows the measures taken at each assessment study visit.

**Table 2 T2:** Measurement scheme

	**Instrument**	**T0**	**T1**	**T2**
**Baseline measures**				

Socio-demographics	Questionnaire	X		
Psychiatric diagnosis	SCID-I	X		
Chronic physical conditions	Check list	X		

**Effect evaluation**				

Compliance	Medication intake percentage	Continuous registration		
Compliance	MAQ		X	X
Severity of depression	PHQ-9	X	X	X
Health-related quality of life	EuroQOL-5D	X	X	X
Anxiety (state)	STAI-S	X	X	X
Side-effects	Check-list		X	X
Satisfaction	Armando PD questionnaire		X	X

**Economic evaluation**				

Direct and indirect costs	CSRI – adapted	X	X	X

T0 = Baseline, T1 = 3 months after baseline, T2 = 6 months after baseline.

SCID-I: Structured Clinical Interview Axis I DSM-IV; MAQ: Medication Adherence questionnaire; PHQ-9: Patient Health Questionnaire 9-item depression module; EuroQOL-5D: European Quality of Life Scale – 5 domains; STAI-S: State-Trait Anxiety Inventory (State subscale); CSRI: Client Service Receipt Inventory.

Clinical diagnosis is made using the research version of the Structured Clinical Interview for DSM-IV Axis I Disorders (SCID-I) [24,25]. Patients are interviewed in the modules of major depression (present and past), dysthymic disorder, anxiety disorder and adjustment disorder as defined according to DSM-IV criteria. Due to the pragmatic character of the study, GPs are blind to the DSM-IV diagnosis and patient inclusion and follow-up is performed according to their usual practice.

The primary outcome measure of our study is adherence to prescribed antidepressant medications, which is assessed through two methods:

1) pharmacy records: every time a patient buys their medication, the pharmacist registers the date of prescription, the date of dispensation and the number of pills dispensed. At 3 and 6 months from baseline, the patient is asked to present the stock of antidepressant medication and any surplus antidepressants following a GP recommended change in medication. To minimize bias, the patient is not told that the aim is to assess compliance. The pharmacist registers the stock of every medication and the percentage of medication intake is calculated by formula: (Number of doses removed/Number of doses prescribed)*100. Poor adherence is defined as taking less than 80% of the prescribed doses. There are two disadvantages of measuring adherence this way: the patient can remove pills but not take them, and this formula does provide information about the timing of the dose removal.

2) self-reported: adherence to prescribed antidepressant medications is assessed with the 4-item scale developed by Morisky et al [26]. The scale asks patients to respond "yes" or "no" to a set of 4 questions. A positive response to any question indicates a problem with adherence. Patients who respond "yes" to any of the items are categorized as non-adherent.

Clinical severity of depression is measured with the Patient Health Questionnaire 9-item depression module (PHQ-9) [27-29]. The PHQ-9 is a nine-item scale that assesses the depression symptoms of the Diagnostic and Statistical Manual of Mental Disorders (DSM-IV). Each of the nine items is scored from 0, not at all, to 3, nearly every day. The PHQ-9 can be used as a screening tool, with summed score ranging from 0 (no depressive symptoms) to 27 (all symptoms occurring daily). Summed scores of 0 to 4 correspond to minimal symptoms; 5 to 9 to mild symptoms; 10 to 14 to moderate symptoms, 15 to19 to moderately severe; and 20 to 27 to severe symptoms.

As mental disorders have been shown to be frequently comorbid in the general population in Spain, and the association between major depression and anxiety has been especially highlighted [4,30], it is recommended that comorbidity be taken into account when treating mental disorders. The State-Trait Anxiety Inventory (STAI) [31,32] is a 40 item self-report measure of state and trait anxiety. Total scores on the state subscale (STAI-S) (20 items) range between 0 and 60, with the higher scores indicating more severe state anxiety. STAI-S is administered in the present research to monitor comorbidity with depression and anxiety clinical severity.

Health-related quality of life is evaluated using the Spanish version of the EuroQol-5D (EQ-5D) [33-35]. The EQ-5D questionnaire is a generic instrument of health-related quality-of-life. The first of the two parts records self-reported problems in one of five domains-mobility, self-care, usual activities, pain/discomfort and anxiety/depression-divided into three levels of severity corresponding to; no problems, some problems, and extreme problems, thus generating 245 possible health states [36]. Each state corresponds to a single index value referred to as the tariff. Value 1.000 is the best health state and value 0.000 corresponds to being dead, 82 of the 245 states have negative values, and are thus rated as being worse than dead [36]. The second part records the subject's self-assessed health on a Visual Analogue Scale (VAS); a vertical 20 cm line on which the best and worst imaginable health states score 100 and 0, respectively.

Satisfaction with the treatment received from the pharmacist is measured with the patient satisfaction questionnaire developed by Armando PD et al [37]. This instrument consists of 10 closed questions using a 5-point Likert scale from 1 (total disagreement) to 5 (strong agreement) and an open section to express comments.

Evident side-effects are assessed using a brief version of the UKU [38] considering the most common side-effects of antidepressants. Those side-effects are listed in Table 3. For each side-effect the intensity (Not present, mild, moderate, or severe), frequency (high or low) and causal relation with antidepressant drugs (yes, no, or unclear) is assessed.

**Table 3 T3:** Assessed side-effects

Asthenia/Lassitude/lncreased Fatigability
Sleepiness/Sedation
Tension/lnner Unrest
Increased Duration of Sleep
Reduced Duration of Sleep
Increased Dream Activity
Tremor
Increased Salivation
Reduced Salivation
Nausea/Vomiting
Diarrhoea
Constipation
Stomach cramp
Orthostatic Dizziness
Palpitations/Tachycardia
Headache
Increased Tendency to Sweating
Weight gain
Weight loss
Diminished Sexual Desire
Sexual dysfunction

Chronic physical conditions are assessed using a "yes" or "no" check-list of 28 illnesses with the potential to become chronic, and an open section for additional illnesses not considered by the authors of the list [39]. Physical conditions considered chronic are listed in Table 4.

**Table 4 T4:** Assessed chronic physical conditions

Chronic Allergy
Arthritis/Rheumatism
Bronchitis/Emphysema
Asthma
Diabetes
Migraine/Chronic headaches
Chronic Back Pain.
Chronic Neck Pain
Vascular Diseases
Heart attack/Angina Pectoris
Heart diseases
Stroke
Varicose veins
Hypertension
Peptic or Duodenal Ulcer
Hemorrhoids
Chronic constipation
Psychological problems/Depression
Cataract
Vision impairment
Hearing impairment
Thyroid Diseases (Hiperthyroidism/Hypothyroidism)
Nervous System Diseases (Multiple Sclerosis, Parkinsonian Disorders, Epilepsy...)
Cancer
Acquired Immunodeficiency Syndrome/HIV Infection
(If male) Prostatic Diseases
(If female) Menopause

Additionally, patients are asked for socio-demographic details including age, sex, marital status, living arrangements, education, employment and type of contract.

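### The pharmacy-record component of the primary outcome rests on a stock count made by unblinded pharmacists from the team delivering the programme, and the blinded-assessment statement does not cover it

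*Protocol article*

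**What the plan says.** Under Measurements, the article states: "The primary outcome measure of our study is adherence to prescribed antidepressant medications, which is assessed through two methods". The two methods are pharmacy records and a four-item self-report scale.

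For the pharmacy records, at each purchase "the pharmacist registers the date of prescription, the date of dispensation and the number of pills dispensed". At 3 and 6 months the patient presents remaining tablets, and then "The pharmacist registers the stock of every medication and the percentage of medication intake is calculated by formula". The formula divides doses removed by doses prescribed and multiplies by 100. One safeguard is given for this method: patients are not told that the purpose is to assess compliance.

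On who these pharmacists are, Setting says that "13 pharmacies with a total of 34 pharmacists will be responsible for providing patients with the intervention and usual care". Under Enrolment, randomization and allocation, when the patient hands over the prescription, "they open the envelope and create a patient study chart distinguishing between control and intervention group".

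On blinding, the same section says that participants and pharmacists cannot be blinded, but that "the assessment visits and data analysis are conducted by independent and blinded evaluators". Measurements repeats that the three visits are held by blinded interviewers, identifies them as two trained psychologists, and adds: "Participants, pharmacists and GPs are not blinded".

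Sample size rests on a 17-point difference in percentage of medication intake. The economic evaluation uses adherence as its measure of benefit, without saying which of the two methods supplies it.

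**The concern.** The blinding paragraph admits that pharmacists are unblinded and offers blinded evaluators as the counterweight. For percentage intake that counterweight is missing, because the observation is made by a pharmacist who knows the arm. Blinded analysis cannot repair a count that was recorded unblinded.

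The recorder also belongs to the team whose programme is under test. A leftover tablet that is not counted is treated as taken, so lenient counting in the intervention arm would raise apparent adherence there. What is at stake is the comparison on which the trial is powered and probably the effect side of the incremental cost-effectiveness ratio. The article says it would recommend implementation if both effectiveness and cost-effectiveness are shown.

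Neither the two disadvantages of the method listed under Measurements nor the validity threats in the Discussion (variability and contamination) mention unblinded recording.

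**Working it through.** **Which data are covered by blinding**

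| Item | Who records it | Knows the arm? |
|---|---|---|
| Tablets dispensed | Pharmacist | Yes |
| Stock at 3 and 6 months | Pharmacist | Yes |
| Four-item self-report (Table 2: T1, T2) | Psychologist at the visit | No, but the respondent does |
| Analysis | Blinded evaluator | No |

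Table 2 lists percentage intake as continuously registered, with no mark at the 3- or 6-month visit. That agrees with the text: this measure lies outside the blinded visits.

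**The plan's own figure.** The total of 194 cannot be reproduced directly, because no standard deviation (SD) is given. It can be back-solved as a comparison of two means:
- Evaluable per arm after 20% dropout: 194 × 0.8 / 2 = 77.6.
- Two-sided 0.05 and 80% power: SD = 17 / [(1.960 + 0.842) × √(2/77.6)] = 37.8 points.
- With whole patients per arm, SD 37.5 gives a total of 193 and SD 38 gives 198.

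The point does not depend on this figure. It only sets a scale for the illustration below.

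**Shift for one patient.** I take doses removed as dispensed minus stock, one dose a day and 180 doses over 6 months. Pack sizes are also assumptions, as the documents give none.
- One uncounted 28-tablet pack: 28/180 = 15.6 points.
- One uncounted 14-tablet blister: 14/180 = 7.8 points.

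At 3 months, with 90 doses prescribed, each shift doubles.

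**Shift in the arm difference.** This equals the difference between arms in the proportion of patients with such a loss, multiplied by the shift per patient. At 6 months:

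| Difference in proportion | 28-tablet pack | 14-tablet blister |
|---|---|---|
| 0.10 | 1.6 points | 0.8 points |
| 0.20 | 3.1 points | 1.6 points |
| 0.33 | 5.1 points | 2.6 points |

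Against the 17-point target, 1.6 points is 9% (1.6/17) and 5.1 points is 30% (5.1/17).

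**Effect on the false-positive rate.** Assume no true effect, 77.6 evaluable patients per arm and a two-sided 0.05 test. With standard error SE = SD × √(2/77.6) and bias b, the rate is 1 − Φ(1.96 − b/SE) + Φ(−1.96 − b/SE).

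| SD (assumed) | b = 2 | b = 5 |
|---|---|---|
| 25 | 7.9% | 23.8% |
| 30 | 7.0% | 18.0% |
| 37.8 | 6.3% | 13.1% |
| 45 | 5.9% | 10.6% |

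A small recording difference does little harm. One of 5 points at least doubles the nominal error rate across these SDs.

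**The case against.** The strongest reply is that nothing is hidden. The article says openly that pharmacists are unblinded and claims blinding only for the visits and the analysis. A reader might infer that the plan contradicts itself on blinding. It does not: both statements can be true, and the gap is that the assurance does not reach this measure.

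A reader might also infer that the whole primary outcome is recorded unblinded. The documents do not support that, because the self-report component is collected at the blinded visits. It is only partial cover: the patients are unblinded, and the trial is not sized on it.

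A third tempting reading sets the 15.6-point pack beside the 17-point target and concludes that one lost pack could explain nearly the whole effect. The first figure is a shift in one patient, the second a difference between groups. To move the arm difference by 15.6 points, every intervention patient and no control patient would have to lose a pack from the count.

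Other parts of the reply also stand. A tablet count is fairly objective. Withholding the purpose from patients is a real safeguard against hidden stock, although it does nothing about the recorder and may be weaker where patients have been taught about compliance at that pharmacy. The direction of patient-side bias is open: patients who see the pharmacist often might bring their stock more completely, which would lower their measured intake. With 34 pharmacists in 13 pharmacies, the person counting may be a colleague of the one who delivered the sessions, but is still unblinded.

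**Conclusion.** The point holds for the pharmacy-record component only. The article assigns its stock count to unblinded members of the delivery team, its blinding assurance does not extend to that count, and it does not list the risk. Recorder bias towards the programme is plausible, but the documents establish neither its presence nor its size.

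Under the stated assumptions (one dose a day, 28-tablet packs, a 10 to 33 percentage-point difference between arms in uncounted packs), the 6-month arm difference would move by about 1.6 to 5 points. This should be fixed because the measure sizes the trial and the remedy is cheap. It is not a flaw that makes the outcome unusable.

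**What to change.** Have the blinded psychologists record the remaining stock at the 3- and 6-month visits, before the adherence questionnaire and without disclosing the purpose. Limit the pharmacist to the dispensing log and to a back-up count when packs are forgotten. Report agreement wherever both counts exist.

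Reword the blinding statement so that it covers the interview measures and the analysis. List any remaining unblinded recording, and possible under-presentation of stock by patients, as a limitation. No separate rule for blinded calculation of the percentage seems needed: the article does not say that the pharmacist computes it, and the analysis is already stated to be blinded.

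The cost is a change of procedure and a reminder to bring all packs, with no extra staff or visits. There are two downsides: some patients will forget packs, and a count at the interview may hint at its purpose. A blinded counter removes recorder bias but cannot stop an unblinded patient from withholding tablets, so the limitation should be stated even after the change.
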